**Figure 3 figure3:**
[figure not shown]
Flow diagram representing the study design and procedure. WHO: World Health Organization.

### Ethics Approval

Ethics approval for the study has been submitted and is awaiting approval from the WHO Ethics Review Committee (application ID: CERC.0177).

## Results

Recruitment and data collection are estimated to commence in early 2023. The efficacy of the study will be analyzed using an analysis of covariance with posttest open conversation skills as the dependent variable, controlling for pretest scores. Partially completed surveys will be included in statistical analysis whenever possible. As a sensitivity check, analyses will be repeated by excluding participants who complete the study less than 2 SDs below the median completion time as a data quality check.

The primary outcome is open conversation skills. The secondary outcomes are self-efficacy and behavioral intention items. Exploratory analyses will examine the effect of the game on implementation intentions as well as potential covariates or subgroup differences based on sociodemographic information or previous experiences with COVID-19 vaccination conversations.

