**Results:**

Recruitment will commence in early 2023 and will cease once 450 participants complete the study (225 per group). The primary outcome is improvement in open conversation skills. Secondary outcomes are self-efficacy and behavioral intentions to have an open conversation with a vaccine-hesitant individual. Exploratory analyses will examine the effect of the game on implementation intentions as well as potential covariates or subgroup differences based on sociodemographic information or previous experiences with COVID-19 vaccination conversations.

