## Methods

### Participants and Recruitment

Participants will be recruited to play the game via video or push notifications promoting *The Good Talk!* game on social media platforms (eg, WHO chatbot channels) and advertised via other WHO informational campaigns. Recruitment will be open to all interested individuals worldwide but will be limited to English language speakers. Participants will self-subscribe to the study by accessing the WHO game information web page via the public link or when shared by members in their social network. On the game information page, participants will be asked if, in addition to playing the game, they would like to participate in the research element (a similar approach was used to recruit participants to research elements in other serious web-based games [93,95]). Participants who are not interested in participating in the study will be sent directly to play *The Good Talk!* game; otherwise, they will be asked to opt-in to the study after giving informed consent. Participation in the research element of the game will be restricted to individuals aged ≥18 years. Participation in the study is voluntary, and no remuneration will be offered to complete the study.

Previous studies evaluating the effect of similar serious games on the development of competences report small-to-medium effect sizes averaging around f=0.18 [95,100,105]. A power calculation with a small effect size (f=0.18), power of 0.90, and α=.05 for an analysis of covariance on posttest open conversation skills suggests a total sample size of n=327. We will aim to collect 450 responses (225 per condition) to account for potential technical issues or possible poor-quality data. Data collection will continue until the prespecified sample size for each condition is reached. Preregistration of this study can be found on the Open Science Framework [107].

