### Design

Participants who enter the game website and agree to participate in the research study will be randomized to the experimental or control group (between subjects) and complete both a pre- and postgame survey (within subjects). The experimental group will play *The Good Talk!* game, and the control group will play the noneducational game *Tetris*.

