### Strengths and Limitations

*The Good Talk!* game represents an evidence-based behavioral science application based on the theoretical framework of boosting that aims to boost people’s skills and competences rather than target a specific cause of vaccine hesitancy. As such, this approach has the potential to build transferrable skills that can be applied across a variety of situations. Delivering the intervention via a worldwide, publicly available serious game means that it has the potential to reach a broad and diverse audience while using an ecologically valid medium that mimics real-world web-based communications.

Nevertheless, there are potential limitations to the insights that can be drawn from this study. First, as participants will access the study via a public link that is associated with the promotion of the game, it is not possible to blind participants completely from their assigned experimental condition. Although participants will be blinded to their assigned conditions at the initial pretest survey stage, it is not possible to avoid dropouts or potential self-selection to their assigned condition. To limit this effect, all participants will be told that both games are very important for the research and that everyone will get the opportunity to play *The Good Talk!* game. We will also collect data on the number of dropouts and partially complete and completed surveys per condition to evaluate their impact on study completion. Second, the game may attract a diverse set of participants from various backgrounds worldwide, including different levels of English proficiency, experience with COVID-19 vaccination, and social and political contexts. However, as the intention for the game intervention is to reach a broad and diverse audience and be applicable to individuals from a wide range of cultural, economic, and educational backgrounds, the evaluation will also contribute data on the effectiveness of the intervention in a real-world context.

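### The posttest ANCOVA and the stop at 225 completers per condition leave out anyone who quits during the game, and nothing planned corrects or bounds the bias if loss differs by arm

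*Protocol article*

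**What the plan says.** All references are to the protocol article.

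- **Randomisation (Design).** "Participants who enter the game website and agree to participate in the research study will be randomized to the experimental or control group". Strengths and Limitations adds that "participants will be blinded to their assigned conditions at the initial pretest survey stage", so people learn their condition when they meet the game.
- **Primary model (Results).** An "analysis of covariance with posttest open conversation skills as the dependent variable, controlling for pretest scores".
- **Incomplete data (Results).** "Partially completed surveys will be included in statistical analysis whenever possible". The only sensitivity analysis named repeats the analyses without unusually fast completers.
- **Recruitment stop.** The abstract counts completers: recruitment "will cease once 450 participants complete the study (225 per group". Participants and Recruitment adds: "Data collection will continue until the prespecified sample size for each condition is reached". It raises the calculated 327 to 450 for technical problems and poor-quality data, and does not name dropout.
- **Dropout (Strengths and Limitations).** Because people arrive through promotion of the intervention game, "it is not possible to avoid dropouts or potential self-selection to their assigned condition". Two preventive measures follow: everyone is told that both games matter for the research, and everyone is promised access to The Good Talk!. The investigators will also "collect data on the number of dropouts and partially complete and completed surveys per condition".
- **Order of questions (Procedure).** Vaccine support, past conversations, pretest skills, self-efficacy and intention come before the game. Demographics come after the posttest.

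**The concern.** The loss that matters happens during the game, after condition is known and before any posttest item. The sentence on partial surveys can rescue someone who answered some posttest items or skipped the demographics. It cannot give a posttest score to someone who closed the Tetris page. With recruitment counted in completers per condition, each such loss is made good by another completer in the same arm. Equal arms of 225 can therefore hide unequal numbers randomised.

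A mechanism for unequal loss is easy to see. Participants are unpaid, they come because The Good Talk! was advertised, and people who decline the study go straight to that game. If those who stay differ between arms in ways that the pretest score does not capture, the primary comparison is no longer protected by randomisation, and enlarging the sample from 327 to 450 only adds precision around a shifted value.

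**Working it through.** **1. The plan's own figure.** Inputs from Participants and Recruitment: f = 0.18, power 0.90, alpha 0.05. With an exact noncentral F test for two groups, noncentrality f²N and error degrees of freedom N − 3, N = 327 gives power 0.9007. The stated 327 reproduces, so the sample size arithmetic is not at fault. At N = 450 the power is 0.968. For two equal groups d = 2f = 0.36.

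**2. What the quota can hide.** The protocol gives no completion rate, so these are assumptions. To reach 225 completers, an arm must randomise 225 / completion rate:

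- 80%: 225 / 0.8 = about 281
- 60%: 225 / 0.6 = 375

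Both arms would be reported as 225.

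**3. Illustrative bias.** Assume 80% completion for the game and 60% for Tetris. Assume that the propensity to complete is normal and has the same correlation rho, in both arms, with the posttest residual after pretest adjustment. Among completers the mean residual is rho × φ(z_p)/p, where z_p is the normal quantile at p:

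- game, p = 0.8: φ(0.842)/0.8 = 0.350
- Tetris, p = 0.6: φ(0.253)/0.6 = 0.644
- difference, Tetris minus game: 0.294 × rho residual SDs

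The Tetris mean is raised more, so with positive rho the bias runs against the game.

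**4. Effect on the test at 225 per arm.** A shift of b SD moves the test statistic by b × √450 / 2 = 10.61b. Without bias the expected statistic is 0.36 × 10.61 = 3.82. Power is Φ(3.82 − 10.61b − 1.96).

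| rho | bias b (SD) | share of 0.36 | power if d = 0.36 | two-sided rejection if no effect | of which favouring the game |
|---|---|---|---|---|---|
| 0 | 0 | 0% | 0.97 | 0.050 | 0.025 |
| 0.1 | 0.03 | 8% | 0.94 | 0.061 | 0.012 |
| 0.3 | 0.09 | 24% | 0.82 | 0.155 | 0.002 |
| 0.5 | 0.15 | 41% | 0.62 | 0.344 | 0.0002 |

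**5. Reading the table.** In this scenario nearly all the excess rejections favour Tetris, and the chance of a false finding for the game falls below 2.5%. The practical cost is lost power. Reversing the dropout pattern, or making rho negative, reverses the sign. A simulation with a different selection model (an unmeasured motivation affecting both completion and posttest) gave bias of about 0 when both arms completed at 80%, and 0.04 to 0.08 SD against the game at 80% versus 60%.

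**The case against.** Several points on the other side stand.

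- Only a journal article is at hand, and it cites a preregistration. A method for missing posttests may be set out there or in an analysis plan, and its absence from the article is not itself an error. The article never restricts the analysis to completers, and its one sentence on partial data leans towards inclusion. What remains is the stated combination: a posttest outcome, a recruitment stop counted in completers per condition, and conceded self-selection. Any later method has to work with these.
- The protocol does more than count dropouts. The message about both games and the promise of access address the very reason someone might leave Tetris. They may lower loss, but they do nothing for the estimate if loss still differs.
- A pretest-adjusted ANCOVA is unbiased if loss depends only on arm and pretest score and the model is correct. The problem arises only for selection beyond the pretest.

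A reader might infer two stronger claims. One is that the protocol expects, or has built in, dropout driven by condition. The text says potential self-selection and gives no rate or predicted difference. The other is that the plan inflates false claims of benefit. In the scenario most easily argued from the design, with more loss in the Tetris arm and completers scoring higher, the bias goes the other way. A false benefit would need more loss in the game arm or a negative correlation, and the documents support neither.

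**Conclusion.** The point holds in a limited form. As fixed in the protocol, people who leave during the game cannot enter the primary analysis and are replaced within their arm, and no planned step would correct or bound the resulting bias. Its size and direction cannot be derived from the documents, and it is near zero if loss is alike in both arms. The range of 0.03 to 0.15 SD against the game, with power between 0.94 and 0.62 in place of about 0.97, rests wholly on assumed completion of 80% and 60% and an assumed correlation of 0.1 to 0.5; the low end of power needs the strongest correlation. It shows that a moderate imbalance could matter, not that it will occur. This is a worthwhile, inexpensive improvement to make before recruitment begins, not a proof that the primary result will be invalid.

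**What to change.** 1. Define the primary population as all randomised participants, by assigned arm.
2. Report numbers randomised and completing in each arm, and completers' pretest scores by arm.
3. Handle missing posttests by multiple imputation by arm, or by an ANCOVA adjusted for the same variables. Use what is collected before the game: pretest skills, self-efficacy, intention, vaccine support and prior conversations. Imputing from the pretest score alone would only reproduce the completer ANCOVA; the gain comes from the other variables. Demographics can be added only if that survey is moved ahead of the game, because leavers never reach it now.
4. Add a delta-adjusted (tipping-point) sensitivity analysis in which the shift for missing posttests varies by arm.
5. Keep the completer ANCOVA as a supportive analysis.

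Moving randomisation to after the pretest would ensure baseline data for everyone randomised, but it is optional: participants are already blind to condition until then, and the move does not affect loss during the game.

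Cost: wording, a little more analysis work, possibly a slightly wider confidence interval, and one survey page moved if demographics are wanted. No extra participants are needed. Imputation removes only the bias that the measured pre-game variables explain, so the tipping-point analysis is needed as well.

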### Procedure

Participants will first answer the questions regarding their support for COVID-19 vaccination and their past experience speaking with vaccine-hesitant individuals. Participants will then complete a pretest survey containing the 8 open communication skills items and the self-efficacy and behavioral intention items. The experimental group will then play *The Good Talk!* game, which will take approximately 10 minutes to complete. The control group will play *Tetris* for a similar amount of time.

Following the game, participants will respond to a posttest survey containing the open communication skills, self-efficacy, and behavioral intention questions. Participants will also complete the implementation intention questions and a short demographic survey. At completion of the study, participants will be thanked for their time and invited to share the study with their friends. Participants in the control group will be given the option to play *The Good Talk!*. Figure 3 presents the flowchart of the study design and procedure.

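### The speed check (2 SDs below the median completion time) is likely to exclude few or no fast completers once a few sessions are interrupted, and would then only repeat the main analysis

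*Protocol article*

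**What the plan says.** The Results section of the protocol article gives the rule as "excluding participants who complete the study less than 2 SDs below the median completion time as a data quality check", and its role as "As a sensitivity check, analyses will be repeated by excluding participants". Centre (median), spread (SD) and multiplier (2) are therefore fixed. No log scale, trimming of long sessions or idle time-out is mentioned. The natural reading is that people more than 2 SDs faster than the median are dropped, although the wording can be read otherwise.

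The only timing facts are in the Procedure section. The intervention game is one "which will take approximately 10 minutes to complete", and for the control arm "The control group will play *Tetris* for a similar amount of time". No SD or expected total time is given.

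Participants and Recruitment describes a public worldwide link and states that "Participation in the study is voluntary, and no remuneration will be offered to complete the study". The same section treats poor data as a real risk: "We will aim to collect 450 responses (225 per condition) to account for potential technical issues or possible poor-quality data". No other rule for excluding poor-quality responses is stated.

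**The concern.** The median resists extreme values and the SD does not. Elapsed time on an unsupervised web page is bounded below but has no natural upper limit, because people pause, take a call or leave a tab open. Each such session enlarges the SD and pushes the lower cut-off down, so slow participants decide whether fast ones can be detected.

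If the cut-off falls to zero or below, the sensitivity data set equals the main data set among completers, and the two results agree by construction. A reader could take that agreement as evidence that careless responding did not matter, although no careless responder had been removed. Choosing a new threshold after finding the planned one empty would be post hoc.

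**Working it through.** **The plan's own figure.** The only related number that can be reproduced is the sample size: "A power calculation with a small effect size (f=0.18), power of 0.90, and α=.05 for an analysis of covariance", giving 327. With two groups, one covariate and noncentrality N × 0.18², power is 0.8998 at N = 326 and 0.9007 at N = 327. The figure reproduces, and the target of 450 leaves a margin. The plan gives no figure for the cut-off or for the number it would exclude.

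**Step 1: when the rule is empty.** Cut-off = median − 2 × SD. This is at or below 0 exactly when SD ≥ median / 2. No distributional assumption is needed.

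**Step 2: one long session.** Assume a median of 20 min and an SD of 4 or 5 min among the other participants. One session of length x among 450 gives, approximately, SD² = s² + (x − 20)² / 450.

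- x = 240 min, s = 4: 16 + 48,400/450 = 16 + 107.6 = 123.6; SD = 11.1; cut-off = 20 − 22.2 = −2.2 min.
- x = 240 min, s = 5: 25 + 107.6 = 132.6; SD = 11.5; cut-off = −3.0 min.
- x = 480 min, s = 4: 16 + 211,600/450 = 486.2; SD = 22.05; cut-off about −24 min.

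Simulation gives the same values (−2.2, −3.0 and −24.1 min).

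**Step 3: can the rule find fast completers?** All inputs here are assumptions except n = 450. The median is 20 min. Fast completers are 5% of participants, with times uniform on 3 to 7 min (about 22 people). Interrupted sessions have 30 to 180 min added. Two shapes were used for ordinary completers:

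- Shape A: a 10-min minimum plus a lognormal excess with log-SD 0.5.
- Shape B: lognormal with log-SD 0.3 and no minimum.

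Means over 4,000 simulated trials:

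| Shape | Interrupted | Mean cut-off (min) | Cut-off ≤ 0 | Excluded, planned rule | Excluded, log-MAD rule |
|---|---|---|---|---|---|
| A | 0% | 6.0 | 0% | 16.1 | 22.6 |
| A | 0.5% | −0.8 | 55% | 2.9 | 22.8 |
| A | 1% | −5.8 | 85% | 0.5 | 22.6 |
| A | 2% | −13.8 | 99% | 0.02 | 22.7 |
| B | 0% | 5.3 | 0% | 12.5 | 28.7 |
| B | 0.5% | −1.1 | 57% | 2.2 | 28.8 |
| B | 1% | −6.2 | 87% | 0.4 | 28.6 |
| B | 2% | −14.1 | 99% | 0.01 | 28.2 |

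Here 0.5% of 450 is 2.25 people and 1% is 4.5. The log-MAD rule removed every simulated fast completer in every row. It also removed about 0.2 ordinary participants in shape A and about 6 in shape B (28.7 − 22.4 = 6.3).

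**The case against.** The strongest reply is that the documents give no SD, so nobody can say the cut-off will be negative. That stands. A reader might infer that the rule is bound to fail for any right-skewed times. The rows without interruptions show otherwise: the planned rule removes about 13 to 16 of 450. With 2% fast completers in shape A (skewness +1.26) it removes about 9, which is all of them. The failure depends on long sessions or a wide spread, not on skewness alone.

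A reader might also point to smooth lognormal times, where the rule excludes almost nobody. That is not evidence of malfunction, since such a distribution contains no separate group of fast completers to find.

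The rule might further be faulted for not classifying partial surveys, given that "Partially completed surveys will be included in statistical analysis whenever possible". The documents do not support this. The check is confined to people who finish, and Strengths and Limitations provides for counting dropouts and partial surveys per condition.

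Finally, the article condenses a preregistration that is not shown, which may define timing on a log scale or cap idle time. If so, the concern falls away. As published, however, the rule is complete enough to be applied literally, and it contains neither safeguard.

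**Conclusion.** The concern holds conditionally. Applied to raw elapsed times, the check stops working once the SD reaches half the median, and two to five interrupted sessions among 450 are typically enough under the assumptions above. In an unpaid, open web study that many interruptions are likely, so the check will probably exclude few or no fast completers. The assumed values are the 20-min median, the 5% share of fast completers at 3 to 7 min, the interruption lengths and the two shapes. The relation between SD and median needs none of them.

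The consequence is limited to a sensitivity analysis. A reader might infer that the trial's main result is at risk. It is not: the primary analysis of covariance, its data set and the sample size are untouched.

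**What to change.** Before any data are seen, replace the rule in the preregistration with a robust one. The preferred form is to exclude a completer if log(time) < median(log time) − 2 × 1.4826 × MAD(log time), where MAD is the median absolute deviation. This also settles the direction of the cut-off. Report the number excluded in each arm beside the sensitivity estimate, and say plainly if it is zero, so that identical results are not presented as robustness.

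The cost is one sentence and a few lines of code. The downside is that a few genuine fast readers leave the sensitivity analysis: about 0.2 to 6 of 450 in the simulations above.

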## Discussion

### Expected Outcomes

We hypothesize that *The Good Talk!* game will lead to a greater increase in open conversation skills, self-efficacy, and intentions to initiate conversations about vaccination between vaccine advocates and their vaccine-hesitant close ties relative to the control game. We hope that the game will help people to talk to one another so that supportive relationships can be maintained, and over time, opportunities to share with consideration of divergent views may help combat some of the negative social costs of the pandemic. Furthermore, we hope that this study will highlight how serious games can be a promising forum for delivering evidence-based health behavior interventions to the public.

